## Abstract

**Background:**

Neck pain is a costly and common problem. Current treatments are not adequately effective for a large proportion of patients who continue to experience recurrent pain. Therefore, new treatment strategies should be investigated in an attempt to reduce the disability and high costs associated with neck pain. Dry needling is a technique in which a fine needle is used to penetrate the skin, subcutaneous tissues, and muscle with the intent to mechanically disrupt tissue without the use of an anesthetic. Dry needling is emerging as a treatment modality that is widely used clinically to address a variety of musculoskeletal conditions. Recent studies of dry needling in mechanical neck pain suggest potential benefits, but do not utilize methods typical to clinical practice and lack long-term follow-up. Therefore, a clinical trial with realistic treatment time frames and methods consistent with clinical practice is needed to examine the effectiveness of dry needling on reducing pain and enhancing function in patients presenting to physical therapy with mechanical neck pain.

**Objective:**

The aim of this trial will be to examine the short- and long-term effectiveness of dry needling delivered by a physical therapist on pain, disability, and patient-perceived improvements in patients with mechanical neck pain.

**Methods:**

We will conduct a randomized, double-blind, placebo-controlled trial in accordance with the CONSORT guidelines. A total of 76 patients over the age of 18 with acute or chronic mechanical neck pain resulting from postural dysfunction, trauma, or insidious onset who are referred to physical therapy will be enrolled after meeting the eligibility criteria. Subjects will be excluded if they have previous history of surgery, whiplash in the last 6 weeks, nerve root compression, red flags, or contraindications to dry needling or manual therapy. Participants will be randomized to receive (1) dry needling, manual therapy, and exercise or (2) sham dry needling, manual therapy, and exercise. Participants will receive seven physical therapy treatments lasting 45 minutes each over a maximum of 4 weeks. The primary outcome will be disability as measured by the Neck Disability Index. Secondary outcomes include the following: pain, patient-perceived improvement, patient expectations, and successful blinding to the needling intervention. Outcome measures will be assessed at 4 weeks, 6 months, and 12 months by an assessor who is blind to the group allocation of the participants to determine the short- and long-term treatment effects. We will examine the primary aim with a two-way, repeated-measures analysis of variance with treatment group as the between-subjects variable and time as the within-subjects variable. The hypothesis of interest will be the two-way group by time interaction. An a priori alpha level of .05 will be used for all analyses.

**Results:**

Recruitment is currently underway and is expected to be completed by the end of 2017. Data collection for long-term outcomes will occur throughout 2017 and 2018. Data analysis, preparation, and publication submission is expected to occur throughout the final three quarters of 2018.

**Conclusions:**

The successful completion of this trial will provide evidence to demonstrate whether dry needling is effective for the management of mechanical neck pain when used in a combined treatment approach, as is the common clinical practice.

**Trial Registration:**

ClinicalTrials.gov NCT02731014; https://clinicaltrials.gov/ct2/show/NCT02731014 (Archived by WebCite at http://www.webcitation.org/6ujZgbhsq)

## Introduction

Neck pain is common, with 30%-50% of the population afflicted in a given year [1]. Symptoms of neck pain persist longer than 12 months in 37% of patients [2]. Neck pain is ranked fourth highest out of all 291 conditions studied in the Global Burden of Disease 2010 study measured by years lived with disability [3]. In the United States, estimated increases in expenditures for patients with spine pain have increased 65% from 1997 to 2005 [4]. Patients with neck pain account for 10%-20% of all patients seen in outpatient physical therapy [5,6].

Commonly, physical therapists utilize patient education, exercise, mobilization, manipulation, massage, and electrophysical modalities when treating patients with mechanical neck pain. Yet the most recent Cochrane reviews on patient education [7], exercise [8], and manual therapy (ie, joint mobilization [9] and massage [10]) find a lack of high-quality evidence to support these interventions independently. There is some evidence that multi-modal physical therapy treatment consisting of a combination of exercise and mobilization/manipulation seems to be more effective than either intervention alone [11].

Dry needling has emerged as a treatment modality that is widely used in the clinical environment to address a variety of musculoskeletal conditions including neck pain [12-14]. Dry needling is growing in popularity despite a lack of clinical trials examining its effectiveness, likely due to the ease of applying dry needling in a clinical setting [15,16]. Dry needling is a technique in which a fine needle is used to penetrate the skin, subcutaneous tissues, and muscle with the intent to mechanically disrupt tissue without the use of an anesthetic [17].

Most commonly, dry needling targets myofascial trigger points (MTrPs), which are described as localized hypersensitive spots in a palpable taut band of muscle [18-28]. These hyperirritable spots can be classified as active MTrPs when they produce spontaneous pain and, when palpated, reproduce a patient’s familiar pain. Latent MTrPs do not produce spontaneous pain and are only painful upon palpation [29]. Many studies have shown that MTrPs are prevalent in patients with chronic neck pain [30-34]. It has been reported that MTrPs in the neck and shoulder commonly result in limited range of motion in the neck, neck pain, headache, and dizziness [28,33,35].

There have been five recent studies examining dry needling performed by a physical therapist for patients with neck pain. Four of the trials examined the short-term effectiveness of dry needling: three in chronic mechanical neck pain [21,24,28] and one in acute mechanical neck pain [23]. The results of these studies demonstrated that dry needling decreases pain intensity and increases pain pressure threshold in the short term; the longest follow-up was 4 weeks. One recent trial examined the long-term effectiveness of dry needling, which was performed on patients with chronic nonspecific neck pain [36]. At 6-month follow-up, the dry needling and passive stretching group demonstrated significant and clinically relevant improvements in pain, disability, and range of motion when compared to passive stretching alone. These results suggest that dry needling warrants further investigation for the treatment of neck pain.

Recent systematic reviews suggest that dry needling can be recommended in the short and medium term to reduce neck and shoulder pain [37] and for musculoskeletal pain [38]. Yet those reviews concluded that there was limited evidence to support dry needling’s effectiveness in the long term for reducing pain or improving function, especially when compared to other physical therapy interventions. Both authors recommended further studies with adequate sample sizes to examine dry needling effectiveness in both the short and long term on reducing pain and improving function.

The majority of the studies included in the recent reviews compared dry needling to control, sham, or to another intervention directly. Not only is this not consistent with how dry needling is commonly used clinically by physical therapists, but emerging evidence suggests that dry needling, when performed in combination with other interventions, may be more effective at reducing lower back pain than when performed alone [39]. This suggests that dry needling, when combined with other interventions (ie, multi-modal treatment), may result in an improved treatment effect when compared to dry needling performed in isolation.

The majority of existing studies lack adequate sample sizes, only collect short-term outcomes, frequently examine dry needling as a stand-alone intervention, and only treat one muscle for one to two sessions, which is not consistent with how dry needling is commonly performed clinically. Typically, clinicians will perform an examination to locate active and latent MTrPs and needle numerous active trigger points in a single session. They may then dry needle the patient over many sessions to achieve optimal effects. With the high prevalence of neck pain and its contribution to prolonged disability in patients, it is essential to identify optimal treatment approaches [1-3,5,6,40,41]. Therefore, the aim of this randomized clinical trial is to examine the long-term effects of a combination of manual therapy, exercises, and dry needling to the cervicothoracic region on pain and disability in individuals with acute or chronic mechanical neck pain resulting from postural dysfunction, trauma, or insidious onset who are referred to physical therapy.

We hypothesize that patients who receive dry needling, manual therapy, and exercise will achieve greater reductions in pain and disability in the short term (ie, 4 weeks) and long term (ie, 6 and 12 months) compared to those who receive sham dry needling, manual therapy, and exercise.

## Methods

### Design

We will conduct a randomized, double-blind, placebo-controlled trial according to the CONSORT guidelines (see Figure 1) [42,43]. Approval by both the Institutional Review Board at Concord Hospital (Concord, NH, USA), where the trial will be performed, and the University of Newcastle Human Research Ethics Committee (Callaghan, Australia), where the primary author ([name]) is currently enrolled as a PhD candidate, have been obtained. Consecutive subjects presenting to Concord Hospital physical therapy clinics (Concord, NH, USA) and Franciscan St. Francis Health physical therapy clinics (Indianapolis, IN, USA) with mechanical neck pain will be screened for eligibility criteria.

**Figure 1 figure1:**
[figure not shown]
Flowchart of the study trial.

### Subjects

Each physical therapy clinic, upon receiving a patient referral for neck pain, attempts to schedule the patient with the therapists who have agreed to assess and treat participants in the trial. Upon arrival for their initial assessments, patients are informed about the potential opportunity to participate in the study if they meet inclusion/exclusion criteria. A combination of physical examination and self-report measures will be used to assess each patient’s potential eligibility to participate. Inclusion criteria for the study include the following: aged 18 years or older, a primary complaint of neck pain, and a Neck Disability Index (NDI)>10 points=20% [44]. Patient exclusion criteria include the following: red flags (ie, tumor, fracture, metabolic diseases, rheumatoid arthritis, osteoporosis, prolonged history of steroid use, symptoms of vertebrobasilary insufficiency, pregnancy, cervical spinal stenosis, or bilateral upper extremity symptoms); use of blood thinners; history of whiplash injury within the past 6 weeks; evidence of central nervous system involvement, including hyperreflexia, sensory disturbances in the hand, intrinsic muscle wasting of the hands, unsteadiness during walking, nystagmus, loss of visual acuity, impaired sensation of the face, altered taste, or the presence of pathological reflexes such as positive Hoffman’s and/or Babinski reflexes; two or more positive neurologic signs consistent with nerve root compression (ie, muscle weakness involving a major muscle group of the upper extremity, diminished upper extremity muscle stretch reflex, or diminished or absent sensation to pinprick in any upper extremity dermatome); prior surgery to the neck or thoracic spine; workers’ compensation or pending legal action regarding their neck pain; insufficient English-language skills to complete all questionnaires; and inability to comply with treatment and follow-up schedule.

If a patient is determined to have met inclusion/exclusion criteria, they will be asked if they would like to participate in the study. If they choose to provide informed consent, each patient will complete the baseline questionnaires as well as the baseline outcome assessments. Demographic information will be collected for descriptive purposes, including age, gender, employment status, past medical history, mechanism of injury, location and nature of the patient’s symptoms, number of days since onset, number of previous episodes of neck pain, and treatment for previous episodes. Once patients are admitted to the study, no patient will be removed from the study for noncompliance and an intention-to-treat analysis will be used.

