### Intervention

#### Overview

Once the baseline examination is complete, equal numbers of patients will be randomly assigned to one of two groups: (1) manual therapy, exercise, and dry needling (MTEX-Needle group) or (2) manual therapy, exercise, and sham dry needling (MTEX-Sham group). A random-number generator will be used to conduct the randomization. The randomization procedure will be conducted prior to the initiation of the study using a computer program randomizer by an individual not involved in patient recruitment. The randomization will be concealed according to the following procedure. The group assignment will be recorded on a label that will be placed inside an envelope and the envelope will be sealed. After the baseline examination is complete, the randomization envelope will be handed to a treating therapist and treatment will begin according to group assignment. Treatment will be initiated immediately following the baseline examination, unless prohibited by time constraints; in this case, the patient will be scheduled for a follow-up session within 3-5 days to receive the first treatment. Patients in both groups will attend physical therapy for seven treatments over a maximum of 4 weeks. Each treatment session will last for a total of 45 minutes of one-on-one treatment time with the treating physical therapist.

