	After needle is removed, pressure with a cotton ball will be maintained to prevent excessive bleeding
	The number of sites and specific muscles treated will be recorded by the therapist
Trigger point assessment performed on the suboccipital muscles	Patient in prone, therapist identifies the hypersensitive spot in the suboccipital muscles
	The overlying skin will be cleansed with alcohol
	Once the needle has been inserted manually into the trigger point, the needle will be pistoned in an up-and-down fashion so that 2- to 3-mm vertical motions occur (ie, fast-in and fast-out technique as described by Hong) at approximately 1 Hz for 25-30 seconds, with the aim of eliciting local twitch responses
	After needle is removed, pressure with a cotton ball will be maintained to prevent excessive bleeding
	The number of sites and specific muscles treated will be recorded by the therapist

We will compare baseline variables between groups by using independent *t* tests or Mann-Whitney U tests for continuous data and chi-square tests of independence for categorical data. An intention-to-treat analysis will be utilized, in which all participants will be analyzed in the group to which they were originally assigned. All dropouts and the reasons for dropping out of the study will be reported. An a priori alpha level of .05 will be used for all analyses. All data will be checked to ensure they meet the assumptions for the inferential statistical analyses described below. If they do not meet the necessary assumptions, appropriate nonparametric procedures will be utilized. We will examine the primary aim with a two-way repeated-measures analysis of variance with treatment group (ie, manual therapy, exercise, and dry needling vs manual therapy, exercise, and sham dry needling) as the between-subjects independent variables and time (ie, baseline, 4 weeks, 6 months, and 12 months) as the within-subjects independent variable. The hypothesis of interest is the two-way group × time interaction. Bonferroni-corrected post hoc tests will be used to determine difference between group means.

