### Power Analysis

Sample size and power calculations were performed using G*Power version 2 statistical software (Heinrich-Heine- Universität Düsseldorf) based on the minimal clinical improvement of 12 points on the NDI [51,69], assuming a standard deviation of 16 points, two-tailed, and an alpha level of .05. This requires a minimum sample size of 29 subjects per group. A total of 76 patients with a primary complaint of neck pain who meet the inclusion/exclusion criteria and consent to participate will be enrolled into the study. This sample size will yield greater than 80% power to detect both statistically significant and clinically meaningful changes in the NDI; additionally, this will control for dropouts prior to the 4-week follow-up.

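### Symptom duration is recorded before randomisation but left out of the stated primary NDI model, which gives up some precision and protection against chance imbalance in a mixed acute and chronic population

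*Protocol article*

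**What the plan says.** The population is deliberately broad. The Introduction states the aim as the effect "on pain and disability in individuals with acute or chronic mechanical neck pain resulting from postural dysfunction, trauma, or insidious onset". The eligibility criteria under Subjects set no minimum or maximum symptom duration; the only time-related exclusion is whiplash within the past 6 weeks.

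Duration is measured. Subjects says "Demographic information will be collected for descriptive purposes, including age, gender, employment status, past medical history, mechanism of injury", and the sentence continues with days since onset, previous episodes and their treatment. All of this is collected before allocation.

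Its use is limited. Data Analysis compares baseline variables between arms by t, Mann-Whitney or chi-square tests to judge whether randomisation was adequate. The primary NDI analysis is a two-way repeated-measures ANOVA with treatment group "as the between-subjects independent variables and time (ie, baseline, 4 weeks, 6 months, and 12 months) as the within-subjects independent variable". The hypothesis is the group by time interaction, and no covariate is named. On allocation, the Intervention overview says "A random-number generator will be used to conduct the randomization" and names no stratification factor.

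**The concern.** The primary test asks whether the two arms follow different NDI courses over 12 months. A patient a few days into a first episode and a patient with years of pain can be expected to follow different courses whatever the needling does. The Introduction points the same way when it says "Symptoms of neck pain persist longer than 12 months in 37% of patients": by the article's own account, many patients no longer have symptoms at the late visits and a substantial minority do.

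A baseline variable that predicts the time course, is known before allocation and is already on the case record form can do two things in the model. It can remove explained variation from the error term, and it can correct the arm comparison for whatever imbalance in duration chance produces. Listing it as descriptive and testing it for balance does neither. A balance test examines a null hypothesis that correct randomisation makes true, and its p-value leaves the treatment estimate unchanged. If the team waits for such a test and then decides whether to adjust, the primary analysis becomes data-driven.

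**Working it through.** **Inputs from the article (Power Analysis, Intervention overview).** Difference: "minimal clinical improvement of 12 points on the NDI". Spread and test: "assuming a standard deviation of 16 points, two-tailed, and an alpha level of .05". Stated minimum 29 per group; 76 enrolled with equal allocation, so 38 per arm. The article gives neither the acute/chronic mix nor the NDI by duration, so those values are assumptions shown as ranges.

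**1. The plan's own sample size.** n per group = 2 × (1.96 + 0.84)² × 16² / 12² gives 28 by the normal approximation. The exact two-sided t calculation gives 29 per group with 80.1% power, which is the stated figure. With 38 per arm, power is 89.7%. The sample-size calculation is sound and this point does not touch it.

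**2. Chance imbalance in duration.** Assume half the patients are of recent onset. A difference of 8 patients is 8/38 = 21 percentage points.
- Two independent binomials (n = 38, p = 0.5): P(difference ≥ 8 patients) = 0.085; P(≥ 6) = 0.207.
- Exactly 38 recent-onset patients among 76, split 38/38 (hypergeometric): P(≥ 8) = 0.108; P(≥ 6) = 0.251.
- Hypergeometric with a share of 30% or 70%: P(≥ 20 percentage points) = 0.045.

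The probability of a gap of about 20 points is therefore 8-11% at an even mix and about 4% at a 30:70 mix.

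**3. What an imbalance is worth in NDI points.** Shift = imbalance × acute/chronic gap in late NDI. For an assumed gap of 5 to 15 points:
- 20-point imbalance: 0.20 × 5 = 1.0 to 0.20 × 15 = 3.0.
- Typical imbalance at an even mix (standard deviation 0.115): 0.115 × 5 = 0.6 to 0.115 × 15 = 1.7.

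For scale, the standard error of an arm difference at one visit is 16 × √(2/38) = 3.7. Even the 3-point shift is below one standard error, and it is a quarter of the 12-point target.

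**4. Precision from adjustment.** Equivalent gain in sample size = 1/(1 − r²), where r is the correlation of log duration with follow-up NDI beyond what baseline NDI explains (assumed). This is a single-visit approximation to the gain in the interaction test.

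| r | 1/(1 − r²) | Extra patients on 76 |
|---|---|---|
| 0.1 | 1.01 | about 1 |
| 0.2 | 1.04 | about 3 |
| 0.3 | 1.10 | about 8 |
| 0.4 | 1.19 | about 14 |

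**5. Cross-check.** With an even mix, a gap D and a total SD of 16, the variance explained is 0.25 × D²/256. That is 0.024, 0.098 and 0.220 for D = 5, 10 and 15, or r of 0.16, 0.31 and 0.47. The two sets of assumptions are of the same order. Removing that variance raises power at 29 per group from 80% to 81-89%, and at 38 per group from 90% to 90-95%.

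**The case against.** The strongest reply is that nothing here is an error. The mixed population is declared openly and the article calls the trial pragmatic, so an average over acute and chronic patients is what it sets out to estimate. Randomisation balances duration in expectation, and the chance imbalance that remains is already covered by the 5% error rate. The article does not give the relation between duration and outcome. Baseline NDI is already one level of the time factor, so duration may add little beyond it. All of this stands. It limits the point to precision and to balance in the sample actually drawn.

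Three stronger readings are tempting, and the documents do not support them.

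- **Dilution.** A reader might take the 63% complement of the persistence figure, apply it to an assumed half of recent-onset patients, and conclude that a 12-point effect shrinks to 12 × (1 − 0.5 × 0.63) = 8.2. The 37% is not specific to recent onset, and nothing says that patients who resolve show zero effect. The 12 points was also set for the trial population, which is already mixed. If the effect does not vary with duration, the mean effect is not diluted. A covariate would not cure dilution in any case.
- **Case mix deciding the result.** Step 3 shows shifts below one standard error. That is a contribution to noise, and it does not replace the treatment effect as the explanation of the result.
- **Stratification as an omission.** The article names no strata, but a condensed article may leave this to the full protocol, so its silence is not a fault.

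It can also be said that covariates belong in an analysis plan that is not shown. That is only a partial answer, because the article does more than stay silent: it states the purpose for which duration is collected and the factors in the primary model. The point is a proposal to improve that stated method.

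**Conclusion.** The point holds as a modest, nearly free improvement. Duration is recorded before randomisation in a population with no duration limit, is labelled descriptive and is used beyond that only in balance tests, while the stated primary model omits it. The consequence is some lost precision and an uncorrected chance imbalance; there is no systematic bias.

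The sizes in steps 2 to 4 rest on three assumptions with no source in the article: an even acute/chronic mix, a late NDI gap of 5-15 points, and a correlation of 0.2-0.4 beyond baseline NDI. At a correlation of 0.1 the gain falls to about 1%. That duration predicts the NDI course at all is plausible rather than documented.

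**What to change.** Before analysis, and without reference to outcome data by arm, prespecify log days since onset and its interaction with time as a covariate in the primary NDI model. The interaction term is essential: duration as a main effect alone explains differences between patients' average levels and leaves the group by time test essentially unchanged. Use this in place of the baseline significance tests, and describe baseline duration by arm in a table without p-values.

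The cost is a sentence or two in the analysis section and a few degrees of freedom: with four time points, one for duration and three for its interaction with time. No additional data, visits or patients are needed, and eligibility and the sample size stay as they are.
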